## Abstract

**Aims:**

Dapagliflozin has been widely used for the treatment of type 2 diabetes mellitus (T2DM) and heart failure (HF). However, data concerning the association between dapagliflozin and the recurrence of atrial fibrillation (AF), especially in patients following Cox-Maze IV (CMIV), are rare. We aim to explore the effect of dapagliflozin on the recurrence of AF after CMIV with and without T2DM or HF.

**Methods and results:**

The study of dapagliflozin evaluation in AF patients followed by CMIV (DETAIL-CMIV) is a prospective, double-blind, randomized, placebo-controlled trial. A total of 240 AF patients who have received the CMIV procedure will be randomized into the dapagliflozin group (10 mg/day, *n* = 120) and the placebo group (10 mg/day, *n* = 120) and treated for 3 months. The primary endpoint is any documented atrial tachyarrhythmia (AF, atrial flutter or atrial tachycardia) lasting 30 s following a blanking period of 3 months after CMIV.

**Conclusion:**

DETAIL-CMIV will determine whether the sodium-glucose cotransporter-2 inhibitor dapagliflozin, added to guideline-recommended post-operative AF therapies, safely reduces the recurrence rate of AF in patients with and without T2DM or HF.

## Introduction

Atrial fibrillation (AF) is the most common arrhythmia. Based on data from the Framingham Heart Study (FHS), the prevalence of AF has increased three-fold over the last 50 years.^1^ The Global Burden of Disease project estimated a worldwide prevalence of AF of approximately 46.3 million individuals in 2016.^2^ Atrial fibrillation is associated with increased mortality that can lead to reduced cardiac output, promote the occurrence of heart failure (HF), and induce abnormal haemodynamic changes in the left atrium, inducing thrombosis.^3^ The Cox-Maze (CM) procedure, which was developed by James Cox in 1987,^4^ is a procedure in which multiple incisions are created in both the left and right atria to eliminate AF while allowing the sinus impulse to reach the atrioventricular node. This procedure became the gold standard for the surgical treatment of AF,^5^ and the latest iteration was termed CMIV, introduced in 2002, which replaced the previous cut-and-sew method by using bipolar radiofrequency ablation and cryoablation to create a biatrial lesion pattern.^6^ However, AF recurrence remains the Achilles heel of the CMIV procedure, with a reported late AF recurrence rate of up to 20–40% after CMIV.^7^

A new oral hypoglycaemic drug, dapagliflozin, a sodium-glucose cotransporter-2 inhibitor (SGLT2i), was confirmed to reduce the risk of cardiovascular adverse events (AEs) and improve coronary heart disease and HF outcomes in multiple clinical trials.^8^ At present, dapagliflozin has been extensively used for type 2 diabetes mellitus (T2DM) and HF. In addition, previous *post hoc* analyses and meta-analyses reported that dapagliflozin can decrease the incidence rate of new-onset AF.^9–11^ Although data on the associations between SGLT2i and the recurrence of AF are relatively limited, recent trials have reported that SGLT2i can achieve greater suppression of AF recurrence after catheter ablation (CA) in T2DM patients.^12,13^ Nonetheless, it remains unknown whether dapagliflozin can improve the recurrence of AF for patients who need the CMIV procedure and whether it can be routinely used after CMIV for AF patients with and without a history of T2DM or HF.

## Objectives

Accordingly, we are conducting a randomized controlled trial to evaluate whether post-operative oral dapagliflozin can improve AF recurrence after CMIV, regardless of concomitant T2DM or HF.

### Study design

This is a prospective, double-blind, randomized, placebo-controlled trial. The manufacturer of dapagliflozin did not provide any financial support or take part in the design of the study. This study is investigator initiated, and the study protocol was in accordance with the Declaration of Helsinki and approved by the ethics committee of Beijing Anzhen Hospital (No. KS2023017). The study was registered at http://www.clinicaltrials.gov (NCT05816733). The flowchart of enrolment and follow-up is shown in *Figure 1*.

**Figure 1 euad333-F1:**
[figure not shown]
Flowchart of the study. AF, atrial fibrillation; AF/AT, atrial flutter or atrial tachycardia; CMIV, Cox-Maze IV; MACCE, major cardiac or cerebrovascular event.

#### Current status of the trial

The study has not yet begun. The start date of recruitment is expected to be 1 September 2023, and the completion of recruitment is expected by late June 2024.

### Patient population

Patients who were hospitalized in Beijing Anzhen Hospital for CMIV of AF were screened for inclusion with written informed consent was obtained from all participants. Patients aged 18 or older with AF undergoing first-time isolated or concomitant CMIV, regardless of concomitant T2DM or HF, were eligible for inclusion. The CMIV procedure was performed in both concomitant with open heart surgery and a stand-alone procedure at our centre. Patients aged 18 or older with AF undergoing first-time stand-alone or concomitant CMIV, regardless of concomitant T2DM or HF, were eligible for inclusion (concomitant CMIV: symptomatic AF patients undergoing other cardiac surgical procedure; stand-alone CMIV: symptomatic AF patients who have failed medical management and prefer a surgical approach, have recurrent AF after CA or are not candidates for CA). Exclusion criteria were dapagliflozin allergy; hyperthyroidism; acute myocardial infarction, cerebral apoplexy, and other vascular disease during the past 6 months; following heart surgery within the last 3 months; estimated glomerular filtration rate (eGFR) < 45 mL/min; history of oral SGLT2i; estimated survival period < 12 months; pregnant and lactating women; left atrial diameter > 65 mm; and refusing to sign informed consent. Additional inclusion and exclusion criteria are listed in *Table 1*.

**Table 1 euad333-T1:** Main inclusion and exclusion criteria of the DETAIL-CMIV trial

**Inclusion criteria**
Age ≥ 18 years Patients who need first-time stand-alone or concomitant Cox-Maze IV procedure (concomitant CMIV: symptomatic AF patients undergoing other cardiac surgical procedure; stand-alone CMIV: symptomatic AF patients who have failed medical management and prefer a surgical approach, have recurrent AF after catheter ablation or are not candidates for catheter ablation) Patients who have the ability and willingness to abide by all the subsequent review and requirements
**Exclusion criteria**
Dapagliflozin allergy Hyperthyroidism Acute myocardial infarction Cerebral apoplexy and other vascular disease during the past 6 months Following heart surgery within the last 3 months eGFR < 45 mL/min History of oral sodium-glucose cotransporter-2 inhibitors Estimated survival period < 12 months Pregnant and lactating women Left atrial diameter > 65 mm Refusing to sign informed consent

### Randomization and blinding

The random allocation sequence was generated with computer-generated random numbers by the study statistician, and sequentially numbered opaque envelopes containing the treatment allocation were utilized to conceal the sequence. Participants will be randomly assigned 1:1 to dapagliflozin (10 mg once a day) or matched placebo with blocked randomization of 10 patients in each block to ensure balance in the treatment groups in case the study needs to be stopped early. Patients and all study personnel (except the independent study statistician) will be kept blinded to the treatment allocation. The trial will adhere to established procedures to maintain separation between the staff that performs the outcome measurements and the staff that delivers the intervention. Staff members who obtain the outcome measurements will not be informed of the treatment group assignment. The intervention staff members who deliver the intervention will not perform the outcome measurements. The dapagliflozin and placebo are packaged in an identical manner with the same labelling, tablet appearance and schedule.

### Surgical procedure

All the CMIV procedures were performed under cardiopulmonary bypass (CPB) with median sternotomy. To reduce the variation among surgeons, we require the CMIV to be performed by qualified surgeons. After the initiation of normothermic CPB, both sets of pulmonary veins are then bluntly dissected, mobilized, and encircled with a urine catheter. Lesions from right atrial (RA) lesion set are performed on the beating heart and with temperature cooled to 34°C. Then, a small purse-string suture is placed at the base of the RA appendage that is wide enough to accommodate one jaw of the bipolar radio frequency (RF) ablation clamp. An ablation lesion is created along the free wall of the right atrium through the purse string down the aortic side of the RA appendage. A vertical right atriotomy is made extending from the intra-atrial septum up towards the atrioventricular groove near the free margin of the heart (at least 2 cm from the free wall ablation). From the inferior aspect of the incision, the RF ablation clamp is used to create ablation lines up to the superior vena cava and down towards the inferior vena cava. A linear cryoprobe is used to create an endocardial ablation line from the superior aspect of this atriotomy down onto the tricuspid annulus at the 2 o’clock position. All cryoablations are performed for 3 min at a temperature below −60°C. The linear cryoprobe is then inserted through the previously placed purse-string suture, and an endocardial ablation line is created down to the tricuspid annulus at the 10 o’clock position. Next, the left atrial lesion set is performed on the arrested heart after aortic cross-clamping. The heart is retracted, and the left atrial appendage (LAA) is exposed and amputated. Through the amputated appendage, the bipolar RF clamp is used to create a connecting lesion into the left inferior pulmonary vein. The LAA is then oversewn in two layers with a running polypropylene suture. The coronary sinus is marked with methylene blue between the right and the left coronary circulations. A standard left atriotomy is then performed, and the bipolar clamp is used to create ‘roof’ and ‘floor’ lesions from the superior and inferior aspects of the atriotomy to the left superior and inferior pulmonary veins, respectively. The RF ablation clamp is also used to create an ablation from the inferior margin of the atriotomy towards the mitral annulus and across the coronary sinus. As the RF bipolar clamp cannot reach the annulus itself, a bell-shaped cryoprobe is used to make an endocardial lesion to the mitral annulus at the end of the mitral isthmus lesion. To complete the left atrial isthmus ablation, an epicardial cryoablation is performed over the coronary sinus in line with the endocardial lesion. The energy source used for each procedure was AtriCure Inc., West Chester, OH, USA. It was repeated three to four times for every ablation to ensure the transmurality. Concomitant cardiac surgery was performed after ablation; for patients with severe coronary artery disease, coronary artery graft bypass was a priority to ensure sufficient cardioplegic solution perfusion.

### Study intervention and background medication

Following CMIV, patients will be randomly assigned to oral dapagliflozin therapy or matched placebo in blocks of ten. Dapagliflozin will be initiated on the first morning after CMIV at a dose of 10 mg once daily until 3 months post-operation. The start date of the observation will be set as the first intervention date. Patients in both groups will undergo 24-h post-operative rhythm monitoring and will be treated with continuous intravenous amiodarone as the standard of care.

All patients will be treated with amiodarone post-operatively, and this trial will test dapagliflozin added to the background medication after CMIV. Routine oral amiodarone at 200 mg twice a day will be administered for 3 months when the patients leave the intensive care unit. Low molecular weight heparin combined with warfarin will be used during the early post-operative period and then treated with warfarin alone after the international normalized ratio (INR) reaches the ideal value (INR of 2.0–3.0).

### Outcome measurement

Primary endpoint is any documented atrial tachyarrhythmia [AF, atrial flutter or atrial tachycardia (AF/AT)] lasting 30 s following a blanking period of 3 months after CMIV.

Secondary endpoints are as follows: (i) any documented atrial tachyarrhythmia [AF, (AF/AT)] at the 6-month follow-up monitoring session after CMIV; (ii) any documented atrial tachyarrhythmia [AF, (AF/AT)] at the 12-month follow-up monitoring after CMIV; and (iii) major adverse cardiac or cerebrovascular events (MACCEs, including cardiovascular death, malignant arrhythmias, and stroke) at 6 or 12 months after CMIV.

### Data collection

Study visits are scheduled to occur before randomization and at 3, 6, and 12 months; a detailed medical history, a routine blood pressure measurement and physical examination, laboratory testing, and 48- to 72-h Holter monitoring will be conducted at each visit. All patients with arrhythmia-related symptoms, especially after the blanking period, will be encouraged to undergo electrocardiography (ECG) during their symptomatic periods, and such events will be registered with the study investigator. In addition, patients who experience longer-lasting arrhythmia symptoms will be instructed to contact local hospitals and undergo cardioversion within 48 h, and additional monitoring (e.g. extra Holter or event monitoring) will be performed for patients with arrhythmia symptoms who cannot be monitored during an acute episode. All ECGs and Holter monitoring will be reviewed by a blinded study investigator. Peri-operative clinical and baseline data, such as the type of AF, medical history, laboratory results, complications, cardiac ultrasound features, general information about the operation, a record of surgical ablation, post-operative complications, and pre-operative medication, will be collected through the electronic medical record database.

### Adverse events monitoring and interim analysis

Adverse events will be constantly monitored by investigators during the process of the study through regular medical check-ups, and the details will be immediately reported to the principal investigator once an AE occurs, regardless of the causal relationship with dapagliflozin. Only serious AEs and AEs of interest or those leading to premature study drug discontinuation, study drug interruption, or dose reduction are recorded. Adverse events of interest include volume depletion, renal events, major hypoglycaemia, and potential diabetic ketoacidosis.

The collection of cardiovascular events and other serious AEs will be performed by two well-trained staff members, and they will follow up specifically for these events by telephone every month for every participant with a phone number who has given prior consent during enrolment. In addition, participants will also be taught and asked to report whether they have experienced any cardiovascular events or other serious AEs. All captive cardiovascular events and other serious AEs will be adjudicated and graded by two well-trained staff members in order to reach a consensus.

Once 75% of the primary events are confirmed, an interim analysis will be performed by using a Haybittle–Peto rule, and if the superiority of dapagliflozin over placebo is demonstrated for the primary outcome with a sided level of 0.001, early termination of the trial can be recommended. The significance level of the final analysis will be determined by the Haybittle–Peto rule, depending on the actual number of events and the timing of the interim analysis.

### Sample size estimation

According to our published work, the recurrence rate of AF after CMIV is 37.9% in patients without oral dapagliflozin therapy.^14^ A recent study showed that dapagliflozin reduced the recurrence rate of AF by 17.1% after RFCA.^13^ We assume a more progressive effect of 20% relative risk reduction. The two-proportion test power analysis was performed by using PASS 15 software ([name]), and the algorithms were as follows: (i) power calculation method: normal approximation; (ii) alternative hypothesis: two sided; (iii) test type: *Z*-test (unpooled); (iv) power: 0.9; (v) alpha: 0.05; (vi) group allocation: equal (*N*1 = *N*2); (vii) input type: proportions; (viii) P1 (Group 1 proportion|H1): 0.821; and (ix) P2 (Group 2 proportion): 0.621. Therefore, the estimated sample size required to detect a significant difference in the chi-square test between the two groups under the conditions of a significance level of 5% on both sides and a power of 90% is 101 cases per group. Assuming a dropout rate of 10%, the target number of enrolled patients has been set at 120 cases per group for a total of 240 cases for the two groups.

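### The sample size text assumes a 20% relative risk reduction, but 101 per group was computed for a 20-point absolute (52.8% relative) reduction; power for the stated effect is about 22%, not 90%

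*Protocol article*

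**What the plan says.** All the relevant statements are in the protocol article, under Sample size estimation, unless noted.

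- Control rate: "the recurrence rate of AF after CMIV is 37.9% in patients without oral dapagliflozin therapy".
- External anchor: "A recent study showed that dapagliflozin reduced the recurrence rate of AF by 17.1% after RFCA". The scale of that figure, relative or absolute, is not given.
- Assumed effect: "We assume a more progressive effect of 20% relative risk reduction".
- Inputs, as proportions free of recurrence: "P1 (Group 1 proportion|H1): 0.821" and "P2 (Group 2 proportion): 0.621", with an unpooled Z-test and normal approximation.
- Result: "a significance level of 5% on both sides and a power of 90% is 101 cases per group". A 10% dropout allowance is then given as the basis for enrolling 120 per group.

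The Introduction gives a wider background range for the control rate: "with a reported late AF recurrence rate of up to 20–40% after CMIV". Nothing elsewhere in the article corrects or explains the word relative.

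**The concern.** The worded effect and the numerical inputs describe different trials. From 37.9%, a 20% relative reduction leads to 30.3% recurrence, a gap of 7.6 points. The inputs have a gap of 20 points. Both cannot be the design assumption, and the 90% power belongs to only one of them.

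The sample size paragraph tells readers which effects the trial was built to detect. Taken at face value, it promises 90% power for a modest benefit, so a null result could be read as evidence against such a benefit. The wording also hides how optimistic the real assumption is. The inputs require dapagliflozin, added to amiodarone in all patients, to cut recurrence by more than half. The anchor is a catheter-ablation study that the Discussion describes as being in patients with T2DM, whereas this trial enrols patients with or without it.

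**Working it through.** **Inputs (Sample size estimation).** Control recurrence 0.379, so 0.621 free of recurrence; other group 0.821 free, so recurrence 0.179; two-sided alpha 0.05 (z = 1.960); power 0.90 (z = 1.2816); equal groups; 120 enrolled per group with 10% dropout, so 120 × 0.90 = 108 evaluable.

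**Step 1: reproduce the plan's figure.** Unpooled normal approximation:

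n = (1.960 + 1.2816)² × [p1(1−p1) + p2(1−p2)] / (p1−p2)²

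= 10.507 × (0.821×0.179 + 0.621×0.379) / 0.20²

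= 10.507 × (0.14696 + 0.23536) / 0.04 = 100.4, rounded up to **101 per group**. This matches the protocol.

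**Step 2: the effect behind that figure.** Absolute: 0.379 − 0.179 = 0.20. Relative: 0.20/0.379 = **52.8%**.

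**Step 3: the effect as worded.** A 20% relative reduction gives 0.379 × 0.80 = 0.3032, a difference of 0.0758. Then

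n = 10.507 × (0.379×0.621 + 0.3032×0.6968) / 0.0758² = 816.8, so **817 evaluable per group**, or 817/0.90 = 908 enrolled per group.

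**Step 4: power at the planned size.** Standard error = √{[p1(1−p1) + p2(1−p2)]/n}. Power is the normal probability below difference/SE − 1.960, plus the negligible opposite tail. At n = 108 and the worded effect, SE = 0.0643, the ratio is 0.0758/0.0643 = 1.179, and power is 0.218.

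| True recurrence, control vs dapagliflozin | n = 101 | n = 108 | n = 120 |
|---|---|---|---|
| 37.9% vs 17.9% (20 points; the inputs) | 90% | 92% | 94% |
| 37.9% vs 30.3% (20% relative; the wording) | 21% | 22% | 24% |

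**Step 5: could another reading rescue the wording?** If the 20% is a relative gain in freedom from recurrence, 0.621 × 1.2 = 0.745. Power at 108 is 51%, and 90% power needs 290 per group. Of the readings tried, only the 20-point difference gives 101.

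**Step 6: sensitivity (secondary).** At 108 per group:
- If the cited 17.1% is absolute (37.9% to 20.8%), power is 80%. If it is relative (37.9% to 31.4%), power is 17%.
- If the 52.8% relative effect is kept but control recurrence is 20% or 30%, within the Introduction's range, power is 60% or 82%.

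**Step 7: dropout.** 101/0.90 = 112.2, so 113 per group would suffice. Enrolling 120 covers 1 − 101/120 = 15.8% attrition, not just 10%.

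**The case against.** The best defence is that relative is a slip for absolute. Both proportions are printed, 101 follows exactly from them, and on that reading the number, endpoint, alpha and test all stand, with 92% power at 108 per group. The document does not show which meaning was intended, so it is fair to say that the 22% describes the stated effect and not necessarily the intended one. This is why the remedy leaves enrolment alone. It does not remove the contradiction: the sentence is wrong as printed, and it makes a very large assumed effect look modest.

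Further points have some force. The protocol openly calls its effect more ambitious than the cited study, so exceeding 17.1% is not in itself an error. The 37.9% control rate comes from the team's own published work and lies inside the background range, and holding the relative effect at 52.8% for other control rates is a choice made for this check. Enrolling more than 113 per group does no harm. These items are context, and the conclusion does not depend on them.

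It is also true that what a null result excludes is judged from the confidence interval, not from planned power. Even so, readers do use the sample size paragraph for this purpose, and here it would mislead them. Finally, the primary analysis is a chi-square test, whereas the check uses the protocol's unpooled Z. With pooled variance the power is 21.5% at 108 and the required number is 820 per group, so nothing changes.

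**Conclusion.** The concern holds and needs correcting. The 90% power belongs to a fall in recurrence from 37.9% to 17.9%, not to the 20% relative reduction that the text claims. For the effect as worded, power is 21% to 24% across 101 to 120 per group (22% at 108), and 90% power would take about eight times the calculated size (817 against 101). These figures assume the protocol's control rate of 37.9%, two-sided 0.05, equal groups and the normal approximation. The arithmetic from the inputs to 101 is correct; the error is the mismatch between the description and the inputs.

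**What to change.** In Sample size estimation, replace the effect sentence with a statement that the calculation assumes a 20 percentage-point absolute reduction in recurrence, from 37.9% to 17.9% (52.8% relative). In the same paragraph:

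- State that, with 108 evaluable per group, power is about 22% for a 20% relative reduction and about 80% for a 17.1-point reduction. Present the latter as an illustration unless the sponsor confirms the scale of the cited 17.1%.
- State that a non-significant result will not be read as excluding a 20% relative reduction.
- State that 120 per group covers 15.8% attrition, since 10% would need only 113.

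This requires one paragraph of wording and no change in enrolment. The price is that the assumed effect becomes visibly more optimistic. If the sponsor did mean a 20% relative reduction, rewording is not enough and the sample size has to be recomputed.
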